### Participants

Three participant cohorts will be recruited: (1) young and healthy (n =35); (2) older and healthy (n =35); and (3) with SCI (n =35). This study protocol is being supported by a Medical Research Council grant (MR/X019144/1). As part of this grant, 2 distinct experimental protocols have been designed: (1) this study protocol, which aims to investigate temperature modulation of shearing forces at the heel; and (2) our companion study protocol (Gordon et al [35]), which aims to investigate temperature modulation of sustained mechanical loading at the sacrum [35]. The separation of the protocols is motivated by their intrinsic conceptual differences (ie, the pathophysiology of shearing-induced vs loading-induced mechanical damage) as well as by different experimental challenges associated with their delivery (ie, the development of a large, shearing-inducing, and thermally controlled friction rig for the heel vs a small thermomechanical indenter for the sacrum). By design, the same participant cohort will be recruited to evaluate regional differences in responses (sacrum vs heel) and assess how the addition of shear force may impact local tissue physiology and the efficacy of cooling.

The sample size justification for this protocol is based on the power calculations from Gordon et al [35], using changes in the peak hyperemic response, which is a robust, repeatable response. Specifically, we will recruit a minimum of 18 participants per group, with target recruitment of 35 individuals, to allow for sufficient statistical power and to account for up to 50% dropout. Participants will be screened for study participation using a set of inclusion and exclusion criteria. The young and healthy participants will be aged 18 to 35 years and the older and healthy participants will be aged 55 to 70 years. The participants presenting with SCI will have an injury level within T1 to S1. The younger and older healthy groups will undertake regular physical activity (1-3 times per week), be nonsmokers and nonvapers, and be free from comorbidities that would preclude them from taking part, such as hypertension or Raynaud's disease. Both male and female participants will be recruited for a subanalysis on the influence of sex; we will also recruit individuals with different skin tones, ranging from light to dark, as assessed by the Fitzpatrick scale [36]. Stratified skin sampling will be used to determine whether there is an influence of skin tone on pressure and shear tolerance at the skin of the heel.

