**Conclusions:**

This analysis will help identify mechanisms of skin damage following repeated shear stress at the heel, furthering our understanding of superficial pressure ulcers. It will also establish physiological and perceptual thresholds for the protective effects of cooling from shearing-induced damage at the heel.

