## Methods

### Overview

Participants will attend 3 experimental sessions separated by a minimum of 24 hours in the Clinical Academic Facility located at Southampton General Hospital (Southampton, United Kingdom). During the sessions, participants will place the center of their posterior heel on a custom-built friction rig with an integrated thermal plate to undergo a standardized protocol eliciting repeated pressure and shear force. The study will use a randomized crossover design involving 3 plate temperatures: 36 ºC (no cooling), 24 ºC (mild cooling), or 16 ºC (strong cooling). Microclimate conditions at the interface between a loaded skin site at risk of pressure ulcer (eg, the sacrum) and a support surface (eg, a mattress) are commonly associated with skin temperatures of approximately 38 ºC. Following pilot testing, some participants (n=2) found a 38 ºC plate temperature to be borderline uncomfortable, so we decided to reduce the plate temperature to 36 ºC to improve thermal tolerability in the no cooling condition. The rationale for using 2 levels of cooling was 2-fold: first, prior research investigating localized cooling on tissue viability in animal models [17,18] used cooling interventions at 25 ºC, demonstrating the benefit of reduced skin temperature in preserving tissue viability. Second, one of the main aims of the study is to examine how different levels of cooling may influence the biophysical properties of the skin and perceptual thermal tolerances of both mild (24 ºC) and strong (16 ºC) cooling.

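### The sacrum-versus-heel comparison cannot separate the effect of shear from the effect of body site, because the two change together along with loading pattern and device

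*Protocol article*

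**What the plan says.** Methods, Participants, gives two purposes for enrolling one cohort in both studies: "evaluate regional differences in responses (sacrum vs heel) and assess how the addition of shear force may impact local tissue physiology". It names the benefit of cooling as well. The same section describes the two studies. One is "this study protocol, which aims to investigate temperature modulation of shearing forces at the heel". The other is the companion, "which aims to investigate temperature modulation of sustained mechanical loading at the sacrum". The equipment differs as well: a large "thermally controlled friction rig for the heel vs a small thermomechanical indenter for the sacrum".

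Within the heel study, participants "undergo a standardized protocol eliciting repeated pressure and shear force" (Methods, Overview). Under Experimental Procedures every session applies 10 shear repetitions at a normal load of 15 N, after a static minute used for thermal preconditioning. The only randomized factor is temperature: "The study will use a randomized crossover design involving 3 plate temperatures" (Overview). The planned model has temperature, time and group as factors (Statistical Analyses).

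The Discussion names the dry aluminum surface as a limitation. It does not mention that site and shear cannot be told apart across the two studies.

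On a lesser matter, the abstract's Conclusions announce: "It will also establish physiological and perceptual thresholds for the protective effects of cooling from shearing-induced damage at the heel".

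**The concern.** A difference in region and an effect of adding shear are two separate quantities. Learning both requires at least one condition in which one factor changes and the other does not, and none is described. A difference between heel and sacrum could come from the skin and tissue of the heel, from shear, from repeated rather than sustained loading, from the device, or from any mixture of these.

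The article itself gives reason not to treat site as negligible. The Introduction describes the posterior heel as thin-skinned and very susceptible to damage. The Discussion notes how little subcutaneous tissue lies there, and says it is unknown whether results from other sites carry over to the heel.

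What is at stake is a mechanistic statement that adding shear changed the tissue response or the benefit of cooling. The two studies together could not support it.

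**Working it through.** **Plan's own figure.** The article gives no figure for the cross-study comparison. Its only reproducible sample-size arithmetic is a minimum of 18 per group with up to 50% dropout: 18 / (1 − 0.5) = 36, against a stated target of 35. That agrees closely and plays no part below, because the problem does not depend on sample size.

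**Inputs.**
- Companion study: sacrum, sustained loading, small indenter; no shear mentioned (Participants).
- This study: heel, repeated pressure with shear, friction rig (Participants; Overview).
- Shear in every heel session: 10 repetitions (Experimental Procedures).
- Temperatures: 36, 24 and 16 °C here (Overview). I assume the same three in the companion, whose temperatures this article does not give.

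**Step 1: the contrast.** At temperature t, let S be the effect of site, H of shear, P of loading pattern and V of device. The expected heel-minus-sacrum difference is

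D(t) = S(t) + H(t) + P(t) + V(t).

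There is one equation and four unknowns at each temperature. An observed D fits S = D with H = 0 exactly as well as S = 0 with H = D.

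**Step 2: the claim about cooling.** The change in that difference from 36 to 24 °C is

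D(24) − D(36) = [S(24) − S(36)] + [H(24) − H(36)] + [P(24) − P(36)] + [V(24) − V(36)].

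Whether shear alters the benefit of cooling is only the second bracket, which is again seen only inside the sum. The same holds for 16 °C.

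**Step 3: rank check.** Take a model with an intercept, site, shear, pattern, two temperature terms, and the interaction of both temperature terms with each of the three factors: 1 + 3 + 2 + 6 = 12 terms. Device is left out, which favors the plan. An effect is estimable only if its contrast lies in the row space of the design matrix.

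| Conditions available | Rank | What can be estimated |
|---|---|---|
| The two studies as described | 6 of 12 | Intercept and temperature terms; no site, shear or pattern effect and none of their interactions |
| Plus a heel condition with the same repeated load and no shear | 9 of 12 | Shear and shear-by-temperature also |
| Plus, instead, a heel condition with sustained load and no shear | 9 of 12 | Site and site-by-temperature also; shear still mixed with pattern |
| Plus both | 12 of 12 | All terms |

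The rank of 6 is 2 studies × 3 temperatures. Across the two studies, the correlation of shear with site is 1.00, and so is that of shear with loading pattern. The lower rows only show what information is absent; they are not a proposal to add sessions.

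**Step 4: can the heel study supply the missing contrast?** The static minute is the only shear-free heel phase. It serves as the baseline for blood flow only (Skin Blood Flow). It always comes first and is also the period of thermal adaptation (Experimental Procedures). A comparison of later repetitions with it mixes shear with time under load and time at temperature. Biomarkers, imaging, conductance and ratings are taken before and after the whole sequence, so they have no shear-free counterpart.

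**Step 5: thresholds.** The gaps between tested levels are 36 − 24 = 12 °C and 24 − 16 = 8 °C. Without modeling assumptions, a change point could only be bracketed within one of them.

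**The case against.** The sentence is a remark under Participants that explains shared recruitment. The Objective and the end of the Introduction are confined to cooling at the heel and its modulation by aging and spinal cord injury, and the planned model has no site or shear term. The sentence names no estimator, and its wording about shear is tentative. The companion protocol is not shown. All of this stands, and it limits the point to one stated purpose. It does not rescue that purpose, since no analysis set out elsewhere can separate factors that never vary apart.

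A reader might infer more than the article supports:

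- *That the study's announced conclusions fail.* They do not fail on this ground. The abstract announces no sacrum-versus-heel conclusion.
- *That the lack of a shear-free heel session biases the temperature comparison.* Load, plate contact and tape sampling are the same in all three randomized sessions, so they do not favor any one temperature.
- *That the two studies differ in duration of loading.* The companion's duration is not given here; only sustained versus repeated loading and the different device are.
- *That three temperatures can say nothing about thresholds.* The word can mean which tested level is protective or acceptable, and the study can address that. Interpolation is also possible under assumptions, though weakly with three levels.

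**Conclusion.** The point holds for the cross-study purpose stated under Participants. On the article's own description, site, shear, loading pattern and device are completely confounded. Neither the site effect nor the shear effect, nor the interaction of either with cooling, can be identified from the comparison of the two studies. Using the same participants removes differences between people but leaves the rank at 6 of 12, and a larger sample does the same.

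This rests on the article's short description of the companion. It would weaken only if the companion contained a sacral shear condition or a shear-free heel condition, and nothing here suggests either. The assumption of common temperatures is not critical: if they differed, temperature would become a further difference between the studies.

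The primary within-heel temperature aims are unaffected. The wording about thresholds is a minor matter of precision.

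**What to change.** 1. In Methods, Participants, state that the cross-study comparison is a combined site-plus-loading contrast and will not be attributed to shear or to region.
2. Add this confounding to the limitations in the Discussion.
3. Keep the study's inference to the randomized temperature contrasts at the heel and their modulation by group. Label any comparison of blood flow during the shear repetitions with the static preconditioning minute as mixed with time under load and cooling time.
4. As a minor change, describe the abstract's thresholds as differences between the three tested temperatures.

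These are changes of wording only. Nothing changes in recruitment, sessions or measurements, so they can be made while data collection continues. The price is a less ambitious claim: the pair of studies would no longer be said to show what adding shear does.

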### Ethical Considerations

This project will recruit and test healthy individuals aged 18 to 70 years as well as individuals with SCI. The project will be conducted in line with the Southampton University Code of Practice for Research, complying with the Declaration of Helsinki. Written informed consent will be obtained from participants, as will relevant personal information (eg, perceptual skin sensitivity to cooling). Participants will have the unconditional right to withdraw from the study at any point.

Data management will adhere to the University of Southampton’ policy on data quality, which forms part of the University’s Information Governance Framework, complying with the requirements of the Data Protection Act 2018 and the University of Southampton’s Ethics Committee (Ethics and Research Governance Online; ERGO) policies. This project involves human participants and will be conducted in line with the university’s policy on the ethical conduct of research and studies involving human participants and the Medical Research Council’s policies on ethics and data sharing. Data will be fully anonymized at the earliest opportunity and before being made available with open access in the university’s data repository. All data that supports publication will be deposited and will be citable using a persistent identifier (DOI). Research findings will be published in high-quality, peer reviewed academic journals.

Participants will be eligible for compensation for their time upon successful completion of an experimental trial in the form of retail vouchers (maximum compensation value: £576 [US $785]). All experimental methods and measurements will be noninvasive, posing low risks to participants. However, mitigation measures are in place to manage any risks that may develop, including on-going skin temperature monitoring, checks of subjective well-being, and active skin rewarming following the cooling stimuli. The skin will also be checked for blanching erythema at regular intervals. Ethical approval for the stated measurements and procedures has been granted by the University of Southampton’s Ethics Committee (ERGO 88984).

### Experimental Procedures

The study uses a repeated measures cohort design. Once participants have been screened and recruited, they will be invited to their randomly allocated experimental sessions [37]. They will come to the laboratory wearing comfortable, loose-fitting attire. Upon arrival, participants will be seated while they acclimatize to the ambient conditions of the laboratory (21-24 °C; 50% relative humidity) before recording height and body mass (Seca 874; Seca GmbH).

Following the pre-experimental checks, participants will be seated on a hospital bed in a semireclined position supported by pillows and a back rest. An elevated ankle cushion (20 × 11 × 10 cm) will then be positioned under the right leg and placed under the gastrocnemius muscle belly. To standardize the position of the foot and ankle and minimize movement during the repeated shear movements, an adjustable orthotic ankle foot brace will be strapped on to the right foot and the ankle angle set to a neutral plantar grade position (90°). This will ensure the skin over the calcaneus is consistently in contact with the surface of the thermal plate when the heel is placed on the friction rig and provide a constant relative tension in the local skin site (Figure 1). The axial load will then be standardized to exert 15 N of normal force on the thermal plate.

**Figure 1 figure1:**
[figure not shown]
Experimental set up. The foot and ankle are supported by an orthotic brace and ankle support to standardize positioning while minimizing movement during the shearing protocol.

A series of measurements that run continuously or during discrete time points will be taken (Figure 2). First, baseline assessments, including structural and functional imaging of the posterior heel skin, will be captured using optical coherence tomography (OCT). This will be followed by sampling of skin sebum at the heel for subsequent biomarker analysis, using an established methodology involving a 2-minute application time and tweezer extraction to avoid cross contamination [38]. To provide an index of baseline local skin hydration, a capacitance meter will then be placed on the heel to measure skin conductance (in microsiemens). After the baseline measurements are completed, participants will place the heel on the thermal plate of the shearing rig [13]. The temperature of the aluminum thermal plate (22 × 16.7 cm) is controlled by a set of Peltier elements, and when applied to the skin, allows for the manipulation of local skin temperature (range 0 °C to >50 °C; variable temperature rates under PID control [Daisylab; MC Computing]). An optical fiber is integrated in the center of the plate through a 1-mm hole flush to its surface, allowing for the monitoring of skin blood flow via laser Doppler flowmetry (LDF) when the heel is static. An integrated force plate and low resistance trackway allow the recording of both normal and tangential forces (in newtons), respectively. The friction rig is interfaced with an analogue-to-digital data acquisition unit (MC Computing), sampling plate surface temperature (°C), normal forces, and tangential forces at 33 Hz. The kinetic coefficient of friction (CoF) according to Amonton’s law [39] can be estimated as the ratio of tangential to normal force and defined as the resistance generated from 2 surfaces rubbing against each other [40].

**Figure 2 figure2:**
[figure not shown]
Standardized repeated shear protocol delivered at the heel. The friction rig will be used to deliver a standardized protocol to induce repeated shear stress under 3 thermal conditions: a control skin temperature with no cooling (36 °C) and 2 cooling temperatures of 24°C and 16°C. During the protocol, a series of noninvasive measurements will be conducted (estimation of skin friction from the ratio of tangential and normal fore and skin blood flow via laser Doppler flowmetry (LDF); inflammatory biomarker sampling from skin sebum; structural and functional imaging via optical coherence tomography (OCT); perceptual assessment of subjective thermal sensation, comfort, and acceptance; and measurement of skin conductance, to be used as an index of local skin hydration) at different time points (identified in the figure by the arrows).

The friction rig has been modified to be situated on a linear rail system that allows bidirectional linear travel. The travel is achieved by a servomotor (Drylin SAW-0630 linear module with motor; Igus), which is fixed to the rig and causes 10 cm of displacement at the heel at a velocity of approximately 3.3 cm/s. The servomotor is equipped with a linear strain gauge (Loadstar RAS1 S-Beam Load Cell; LoadStar) providing measurements on the tangential pull (in newtons) of the shearing rig during the prescribed displacements. Participants will be asked to provide subjective ratings of thermal sensation, comfort, and acceptability using Likert scales (detailed below). At this point, the standardized protocol to cause repeated shearing stress will commence (Figure 2).

The protocol starts by participants placing the heel in the center of the thermal plate over the hole, where the LDF optical probe is located flush to the surface. Positioning of the bed and lower limb will be modified to provide a standardized 15-N axial load on the plate. Skin blood flow will be measured intermittently (accounting for displacement of the heel following the static loading phases) throughout the protocol via LDF (moorVMS-LDF laser Doppler monitor; Moor Instruments). The heel will remain in place for a 60-second thermal preconditioning period to allow for temperature adaptation at the skin interface (at 36 °C, 24 °C, or 16 °C). The repeated shearing sequence will then commence (Figure 2), initially with a 10-second pause, before the servomotor travels in one direction pulling the rig and displacing it by 10 cm, pausing for 1 second, then traveling in the opposite direction, pushing the rig back to the original starting point. This sequence completes one repetition, which is repeated 10 times. After completing the 10 shearing repetitions, participants’ thermal perceptions will be recorded, followed by posttest OCT, skin sebum, and skin conductance measurements.

The sections below provide a description of the measurements to be used during the protocol.

### Measurements

#### Skin Blood Flow

Skin blood flow will be monitored via LDF using a noninvasive optical probe, sampling at a 1-mm tissue thickness [41]. LDF has been validated [42] and widely used to assess changes in blood flow velocity (as an index of changes in flow) over bony prominences, such as the sacrum [21,22,24,43]. The optical probe is integrated within the custom-built friction rig, allowing concurrent manipulation of skin temperature while monitoring changes in skin blood flow prior to the repeated shearing protocol (ie, the thermal preconditioning phase). LDF values during the thermal preconditioning phase will be used to calculate the baseline skin blood flow (taken as the mean average during the 60-second period) and subsequently compared across test shearing repetitions.

#### Biomarkers

Pro-inflammatory biomarkers (interleukin [IL]-1α, IL-1β, TNFα, IL-6, IL-8, and interferon γ [IFNγ]) and anti-inflammatory biomarkers (IL-1 receptor agonist [RA]) will be extracted from skin sebum via the application of Sebutape (Cuderm). This approach has been optimized [44] to ensure both low- and high-abundance proteins can be quantified. In summary, Sebutape is applied to the heel for 2 minutes before the samples are extracted using tweezers and a gloved hand to avoid cross contamination. Stored samples will be coded and stored at –80 °C prior to analysis using standard ELISA (enzyme-linked immunosorbent assay) plates for targeted proteins. The extraction of skin inflammatory biomarkers will use chemical and mechanical stimuli for maximal extraction efficiency. Chemical extraction will involve 0.85 mL of extraction buffer, which consists of phosphate-buffered saline + 0.1% surfactant (dodecyl maltoside). The tapes will then be shaken with the buffer for 1 hour followed by 5 minutes of sonication. A 0.35-mL aliquot will then be used for total protein analysis. The remaining 0.5 mL will be centrifuged for 10 minutes at a speed of 15,000*g* at 4 °C. The supernatants will be discarded and the remaining solution with the pellet briefly vortexed and used for the immunoassay analysis, as prescribed by the manufacturer, using MSD U-Plex kits (MesoScale Diagnostics).

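### The biomarker procedure discards the supernatant that holds the extracted cytokines and assays the pellet with an unstated volume of residual liquid

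*Protocol article*

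**What the plan says.** The Biomarkers section (Methods, Measurements) names seven proteins, six pro-inflammatory and one anti-inflammatory, to be recovered from Sebutape. It sets the goal of the extraction: "The extraction of skin inflammatory biomarkers will use chemical and mechanical stimuli for maximal extraction efficiency". The steps follow in order.

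- "Chemical extraction will involve 0.85 mL of extraction buffer", made of phosphate-buffered saline with 0.1% surfactant.
- Tape and buffer are agitated together for an hour and then sonicated for 5 minutes.
- "A 0.35-mL aliquot will then be used for total protein analysis". This comes before any centrifugation.
- The other 0.5 mL is spun for 10 minutes at 15,000 g and 4 °C.
- "The supernatants will be discarded and the remaining solution with the pellet briefly vortexed and used for the immunoassay analysis".

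The section gives no volume for the liquid kept, mentions no fresh buffer, and gives no reason for assaying the pellet fraction. It does say of the method: "This approach has been optimized [44] to ensure both low- and high-abundance proteins can be quantified".

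**The concern.** Surfactant, shaking and sonication serve to move protein off the tape and into the buffer. A spin then separates particles from that buffer. The text discards the buffer and carries the particles forward, which runs against the purpose of the steps before it.

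The sentence is also unclear in itself. After a spin, the liquid above the pellet is the supernatant. If it has been discarded, the solution said to remain can only be some part left behind, and its size is not given.

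All seven biomarkers pass through this step. The Abstract names the inflammatory response in the objective, and Statistical Analyses lists biomarker expression among the outcomes for the three-way mixed ANOVA. Each participant gives samples before and after shear in three sessions, so six samples. Any variation in handling between those six enters the time and temperature contrasts directly. The Results section reports 43 participants enrolled by February 2025 with analysis under way, so some samples may already have been processed.

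**Working it through.** **1. Volumes.** 0.85 mL − 0.35 mL = 0.50 mL. This reproduces the stated volume for centrifugation.

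**2. Where soluble protein sits after the spin.** From the article: 15,000 g, 10 minutes (600 s), 4 °C. Assumed: globular proteins of 8 to 52 kDa, buoyancy factor 0.27, viscosity 1.57 mPa·s, radius R = 1.2 × 0.066 × M^(1/3) nm with M in daltons, and a 1-cm liquid column.

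Sedimentation coefficient s = M × 0.27 / (N × 6π × viscosity × R), where N is Avogadro's number. Distance = s × 15,000 × 9.81 × 600.

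For 17 kDa, R = 1.2 × 0.066 × 25.7 = 2.04 nm, s is about 1.27 × 10⁻¹³ s, and the distance is about 0.011 mm. The same formula gives 0.007 mm for 8 kDa, 0.014 mm for 25 kDa and 0.024 mm for 52 kDa. The largest is 0.024 / 10 = 0.24% of the column. Soluble cytokine therefore stays in the liquid that the text discards.

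**3. Amount of soluble analyte discarded.** Let r be the volume in mL kept with the pellet. The article does not give it, so a range is shown. Share discarded = (0.5 − r) / 0.5.

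| r (mL) | Share discarded |
|---|---|
| 0 | 100% |
| 0.05 | 90% |
| 0.10 | 80% |
| 0.25 | 50% |
| 0.40 | 20% |

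More than half is discarded only when r is below 0.25 mL.

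**4. Concentration in what is assayed.** Let f be the soluble share of the analyte, with the rest bound to the pellet and re-mixed by the vortex. With no added buffer, the concentration relative to the extract is f + (1 − f) × 0.5 / r. Both f and r are assumptions.

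| f | r = 0.05 mL | r = 0.10 mL | r = 0.25 mL |
|---|---|---|---|
| 1.0 | 1.0 | 1.0 | 1.0 |
| 0.9 | 1.9 | 1.4 | 1.1 |
| 0.75 | 3.25 | 2.0 | 1.25 |

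If everything is soluble, the reading does not depend on r. If 10% is bound to the pellet, two samples left with 0.05 and 0.25 mL differ by a factor of 1.9 / 1.1 = 1.7 with no biological difference between them. At 25% bound, the factor is 3.25 / 1.25 = 2.6.

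**5. Fractions compared.** Total protein is measured on extract before the spin. The cytokines are measured on pellet and residue after it. A ratio of the two would mix fractions.

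**The case against.** A reader might infer that the plan assays the pellet alone, loses most of its cytokines, and so drives low-abundance markers below detection. The case against that reading is strong.

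- The text assays liquid together with the pellet, so some extract is kept.
- An immunoassay reads concentration. Undiluted residue has the same soluble concentration as the whole extract, and pellet-bound protein would raise the reading rather than lower it.
- Loss of more than half by amount needs a retained volume under 0.25 mL, and the article gives none.
- A residual volume that is the same in every sample would act alike before and after shear and at all three temperatures, so bias in the within-participant contrasts is not shown.
- No normalisation of cytokines to total protein is stated.
- The article condenses a method that it describes as already optimised in a cited source. A slip that swaps supernatant and pellet is also possible.

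All of this stands, and it limits the consequences. It does not remove the contradiction. The article chose to specify the step down to volumes, speed, time and temperature, and the fraction it then sends to the assay conflicts with its stated aim. That is a statement to be corrected or explained, not a detail left to a fuller document. The appeal to a cited optimisation does not say which fraction or what volume is meant.

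**Conclusion.** The point holds as a conflict in a stated laboratory step. The liquid into which the cytokines were extracted is discarded, and the pellet is assayed with an undefined amount of residue.

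Two risks follow. If the liquid is nearly all decanted, too little may remain to run the assay. If some analyte is bound to the pellet, the reading changes with the liquid left: 1.9 against 1.1 times the extract at 0.05 and 0.25 mL, taking 10% bound. The first risk depends on the volume kept. The second depends on that volume varying between samples and on the bound share. The article fixes neither quantity.

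Loss below detection is not shown unless the liquid is almost fully removed. The concern about a cytokine-to-protein ratio applies only if such a ratio is used. The document cannot settle whether the laboratory follows the sentence literally, so it is no evidence that any sample was mishandled. Since the whole inflammatory domain rests on this step and a discarded supernatant cannot be recovered, it should be resolved before more samples are processed.

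**What to change.** Reconcile the sentence with the laboratory procedure in one of two ways.

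- State that the immunoassay is run on the cleared supernatant and the pellet is discarded.
- If the optimised method does keep a residue with the pellet, state that volume, hold it fixed for every sample, and give the reason.

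If cytokines are to be normalised to total protein, measure both in the same fraction. Check which fraction and what volume were assayed for samples already processed, and do not pool samples handled differently.

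The cost is one corrected sentence and a check of the laboratory records. No extra participants, visits or samples are needed, unless the check shows that handling differed between batches.
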